### 2.5. Randomization and blinding

A random number list is generated by a computer and consists of 88 random numbers. The random numbers were arranged from the smallest to the largest to obtain the serial number R. It is stipulated that group A (PA) with *R* = 1–22, group B (EMT) with *R* = 23–44, group C (PA & EMT) with *R* = 45–66, and group *D* (control) with R = 67–88. The resulting sequence of random assignments was placed in sequentially coded, sealed, impermeable envelopes. The investigator in charge of recruitment opens the envelope according to the order of patient enrollment and assigns the subjects to the appropriate subject group.

This study is a single-blind design, and only the investigator conducting the assessment is blinded to group assignment. The therapist cannot be blinded due to using the supervised intervention. In addition, blinding of subjects is not feasible due to the difference in intervention methods. All outcome assessments for this study will be conducted by a separate professional therapist who is not involved in any other part of the study. Moreover, participants will be unblinded when any clinical situation associated with adverse events or patient withdrawal occurs.

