**Methods:**

We will conduct a single-blind, prospective, randomized controlled trial to assess the efficacy of the combined intervention (PA & EMT) on USN in an inpatient rehabilitation setting. The study aims to recruit 88 patients with USN after an ischemic or hemorrhagic stroke. Participants will be randomly assigned to the following four groups: (1) PA group (*n* = 22), (2) EMT group (*n* = 22), (3) PA and EMT group (*n* = 22), and (4) control group (*n* = 22). All groups will receive 10 sessions of interventions over 2 weeks, 5 times per week. Blinded assessors will conduct a baseline assessment, a post-intervention assessment, and a follow-up assessment (2 weeks post-intervention). The primary outcome measure will use the Behavioral Inattention Test-Conventional Subset (BIT-C) and Catherine Bergego Scale (CBS) to assess the levels of USN. Secondary outcome measures will assess the patient's ability to perform activities of daily living using the Modified Barthel Index (MBI). Patients who completed all treatment and assessment sessions will be included in the final analysis.

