### 2.10. Dropout criteria

The intervention will be discontinued if the subject meets one or more of the following criteria: (a) the subject has poor compliance and fails to perform the treatment as required, e.g., the subject does not cooperate with the investigator or the subject does not come to treatment on time; (b) medical records are incomplete and affect efficacy or safety evaluation; (c) subject voluntarily withdraws; (d) subject experiences an adverse event (including episodes of ocular pain, headache, and irritability); and (e) the subject has a severely progressive disease or some comorbidity, complications, or specific physiological changes.

Patients who drop out will not be included in the efficacy analysis; if they drop out for reasons such as the occurrence of an adverse event, they will be included in the safety analysis.

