### 2.12. Data analysis

IBM SPSS Statistics for Windows, Version 26.0 (IBM Corp., Armonk, NY, United States) will be used for statistical analysis. 2-tailed *P* < 0.05 will be considered a statistically significant difference. Continuous variables will be expressed as mean with standard deviation or median with interquartile range, whereas categorical data will be expressed as counts and percentages. Baseline comparisons will be used to examine potential differences between 4 groups. Age, time of onset, and MMSE will be analyzed by ANOVA or Kruskal-Wallis test. Sex, cause of damage will be measured using Chi-square tests. The Kolmogorov-Smirnov test will be used to evaluate the normality of distributions. If a normal distribution is confirmed, one-way ANOVA will be used to examine the effectiveness of intervention between the 4 groups at T1, T2, with Bonferroni correction for multiple comparisons as a *post hoc* test. Otherwise, Kruskal-Wallis (non-parametric test) will be used.

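### Blinding is limited to the outcome assessor, so the analyst and those who judge record completeness after treatment are not blinded, though nothing practical prevents it

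*Protocol article*

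**What the plan says.** **Who is blinded.** Section 2.5 of the protocol article: "This study is a single-blind design, and only the investigator conducting the assessment is blinded to group assignment". The section then explains why therapists and subjects cannot be blinded. Outcome assessments are "conducted by a separate professional therapist who is not involved in any other part of the study". Allocation is also open to study staff: "The investigator in charge of recruitment opens the envelope according to the order of patient enrollment".

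**Who is analysed.** Section 2.10: "Patients who drop out will not be included in the efficacy analysis". The abstract agrees: "Patients who completed all treatment and assessment sessions will be included in the final analysis". Among the section 2.10 criteria for removal is that "medical records are incomplete and affect efficacy or safety evaluation". Another is poor compliance, with no threshold. Section 2.11 says that as much data as possible will still be collected on patients who stop or deviate.

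**How it is analysed.** Section 2.12 checks normality with a Kolmogorov-Smirnov test and uses one-way ANOVA at T1 and T2 if normality is confirmed. "Otherwise, Kruskal-Wallis (non-parametric test) will be used". It gives neither the level of the normality test nor what it is applied to (each arm, pooled data or residuals). It does not say whether raw or change scores are compared, whereas section 2.4 sizes the trial on changes in BIT-C and section 2.8.2 speaks of changes.

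**The concern.** A blinded assessor protects the measurements. That does not protect decisions taken once the measurements exist: which patients stay in the efficacy set, which score is compared, and how the normality check is run. By the wording of section 2.5, those who take these decisions are outside the blind. The article gives a reason for not blinding therapists and patients but none for the people who handle the analysis, and none is apparent.

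The main exposure is the analysis set. The record-completeness criterion depends on the effect on the efficacy evaluation, so it can be applied after outcomes are known. If the person applying it sees both arm and outcome, removals can be steered, knowingly or not, toward the combination, and the false-positive rate for the comparison of most interest rises.

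**Working it through.** **Step 1: read the rule.** Only the assessor is blinded, and the assessor takes part in nothing else. So anyone who judges records, settles the analysis set or runs the tests is someone other than the one blinded person. No section extends blinding to the data managers, to those who judge dropouts or to the analyst.

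**Step 2: inputs for the illustration.**
- Patients per arm: 22 (section 2.4). The plan's own arithmetic reproduces: 20 × 1.10 = 22, and 4 × 22 = 88. Section 2.1 gives a total of 72; the illustration uses the 88 of the abstract and sections 2.4 and 2.5.
- Level: two-sided 0.05 (section 2.12), so 0.05 / 2 = 2.5% in the direction favouring the combination.
- Number removed: 1 or 2 per arm. Two is the planned loss, 22 − 20 = 2.
- Assumptions not in the document: no true difference; normal data, or exponential data as a skewed case; a Welch t test of combined versus EMT, without the Bonferroni correction that section 2.12 applies to post hoc tests.

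**Step 3: procedure.** Simulate 20,000 null trials. Count a false positive when the two-sided P is below 0.05 and the combined mean is the higher. A favourable removal of k per arm drops the k lowest values in the combined arm and the k highest in the EMT arm. The comparator drops 2 per arm without regard to arm or outcome.

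**Step 4: results.**

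| Removals per arm | Normal data | Skewed data |
|---|---|---|
| None | 2.3% | 2.2% |
| 2, without regard to arm or outcome | 2.5% | 2.1% |
| 1, favourable | 10.6% | 8.9% |
| 2, favourable | 24.0% | 20.7% |

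The simulation standard error is √(p(1 − p)/20,000): about 0.1 percentage points at 2.3% and 0.3 at 24%. The rise is therefore not noise. It comes from removals informed by arm and outcome, since removing the same number without that knowledge leaves the rate where it was.

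**Step 5: the test branch.** In the same normal-data simulation, the four-group ANOVA alone rejects in 4.8% of trials, Kruskal-Wallis alone in 4.7%, and whichever is significant in 5.9% (skewed data: 4.5%, 4.6% and 6.6%). Even a free pick between the tests adds little, and the plan does not allow a free pick.

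**The case against.** **The article never says that the analyst knows the arms.** 'Only' can be read as contrasting the assessor with the therapist and the subjects, the two parties discussed next. This stands in part: the conclusion is an inference from that word, and no analyst is named. The wording is nevertheless exclusive, and an analysis plan that blinded the analyst would contradict it.

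**Coded arms and lock procedures belong in the SAP.** It is true that operational detail may sit there and is not missing here. The point is the stated limit of the blind in section 2.5, not the absence of a procedure.

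**Freedom over test and score inflates the overall four-group error because the analyst is unblinded.** A reader might infer this, and the document does not support it. Four-group ANOVA and Kruskal-Wallis P values are the same whatever the arms are called. With an assumed baseline-outcome correlation of 0.5 to 0.7, choosing the better of the two tests on raw or change scores rejected in 10.4–11.2% of null trials with arms as issued and 11.0–11.6% with arms recoded. The highest and lowest arms are just as visible under neutral codes. Such figures argue for fixing the choices in advance, not for blinding. The branch is also largely bound by the normality test: following that rule (Lilliefors version in each arm at 0.05, an assumption) gave 5.0% on normal and 4.8% on exponential null data.

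**Removals often happen on treatment, decided by staff who cannot be blinded.** This stands. Section 2.10 introduces its criteria as reasons to discontinue the intervention, and blinding the analyst does not reach those decisions. It reaches only judgements made afterwards, chiefly on completeness of records.

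**The illustration assumes that the least helpful patients are picked deliberately.** This also stands. It is an upper-end scenario; section 2.10 requires records to be incomplete, and section 2.11 has two data managers cross-check the entries.

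**Conclusion.** The point holds as an avoidable weakness in the design. By its stated rule the protocol leaves unblinded the analyst and those who judge record completeness after treatment, while efficacy rests on completers and one removal criterion refers to the efficacy evaluation itself. In the worst case the favourable-direction error for combined versus EMT rises from about 2.3% to about 11% with one steered removal per arm and 24% with two. The figures assume no true effect, removals chosen on both arm and outcome, and an uncorrected pairwise test.

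They show what is possible under the rule. They are no evidence that anyone has made or will make such removals, and the document does not support reading them that way. Nor would blinding the analyst repair the completer-only analysis set, which is a separate matter. The change is worth making because it is cheap; it does not put the trial's measurements in doubt.

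**What to change.** Amend sections 2.5 and 2.12 to state that:
- the two data managers already named in section 2.11 hold the allocation key and release the dataset with arms as neutral codes; as key-holders they do not decide removals;
- the score compared (raw or change), and the level and unit of the normality test, are fixed before outcome data are examined. Coding the arms does not replace this step;
- removals for incomplete records after treatment are decided without arm or outcome in view;
- the key is opened only once the analysis set is locked.

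Section 2.5 should then list the analyst and those who judge record completeness among the blinded, so that 'only' no longer excludes them.

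**Cost.** Wording plus one recoding of the dataset by existing staff. Sample size, treatment and patient burden do not change. Arm-specific checks have to wait until the lock. On-treatment discontinuations judged by unblinded therapists are not cured by this change.

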### 2.6. Interventions

All subjects will receive conventional rehabilitation during the intervention period, as well as appropriate interventions according to the group.

#### 2.6.1. Conventional intervention

Conventional rehabilitation therapy includes physical therapy, occupational therapy, and acupuncture. Physical therapy includes muscle strength and endurance training, joint range of motion training, balance and coordination training, gait training, etc. Occupational therapy includes training in activities of daily living (ADL) (e.g., dressing, eating, brushing teeth, and washing face, etc.). Acupuncture includes acupuncture points such as Baihui, DiCang, Shoulder, Quchi, Hand SanLi, Neiguan, HeGu, LiangQiu, Blood Sea, FengShi, Foot SanLi, YangLingQuan, SanyinJiao, and Taichong.

#### 2.6.2. Prism adaptation

Prism adaptation is a non-invasive, affordable, convenient technique to assess visuomotor plasticity and ameliorate the symptoms of USN (39). During a PA session, the patient wears goggles with prism lenses that induce a deviation of the visual field toward the ipsilesional side of space and perform a series of pointing movements toward a visual target. PA training was performed using a black box with parameters as described by Spaccavento et al. (height = 30 cm, depth = 34 cm at the center and 18 cm at the periphery, and width = 72 cm) (33). The PA process consists of three steps: (1) aiming in the direction of visual targets without goggles to obtain a reference frame (pretest); (2) 90 aiming movements in the direction of visual targets with prisms that deviate from the environment approximately 10**°** to the right or left (prismatic exposure). Initially, the movements are deviated toward the right or left, and then, the subject progressively corrects his errors; (3) aiming toward visual targets without the prisms to measure the after-effects. According to the patient's training performance, the PA training schedule was 15–20 min/session, 1 session/day, and 5 days/week, with a treatment period of 2 weeks.

#### 2.6.3. Eye movement training

The eye movement training will be performed based on a high-performance EMT instrument (Figure 2, Hangzhou Jizhi Medical Technology Co., Ltd., Model: JZ-RZ-20US). The insect shoot-down task of the cognitive rehabilitation training and assessment system will be selected as the EMT task (search and gaze). The insect shoot-down task will be set at easy, moderate, and difficult levels (depending on the patient's training performance), left or right field of view (the choice of left or right visual field depends on the patient's side of neglect), during which the insect will randomly present on the left or right side of the screen and move from bottom to top. Under the guidance of the therapist, the patient spontaneously searches for these signs, eliminates them by gazing, and then searches for the next sign until the end of the training. At the same time, this eye-tracking device has an eye-tracking function, which can visually show the patient's eye movement trajectory and facilitate the therapist to better train the patient. The EMT schedule was 15 min/session, 1 session/day, and 5 days/week, with a treatment period of 2 weeks.

**Figure 2 F2:**
[figure not shown]
Eye movement training device (image from ourselves).

### 2.7. Baseline data

Baseline data are collected after informed consent and before randomization. The baseline assessment includes demographic characteristics such as sex, age, time of onset, cause of damage, and assessment scales including the Mini-Mental State Examination, Catherine Bergego Scale, Behavioral Inattention Test-Conventional Subset (BIT-C), and Modified Barthel Index (MBI). All baseline data will be collected *via* paper forms.

### 2.8. Outcome measures

This study will measure outcome indicators at two time points: after the end of the intervention and 2 weeks after the end of the intervention. The measurement of outcome indicators will be conducted by independent therapists. The relevant test nodes can be seen in the study schedule (Table 1).

#### 2.8.1. Mini-mental state examination

The Chinese version of the MMSE was initially developed by Katzman et al. (40) and later widely used in clinical practice and studies. The test includes cognitive assessments in five domains: time and place orientation, memory, attention and calculation, immediate and long-term memory, and language and comprehension. The total score of the test is 30, and the cutoff points for dementia screening are 16/17 for illiterate, 19/20 for those with 1–6 years of education, and 23/24 for those with 7 or more years of education (41).

#### 2.8.2. Primary outcomes

Two main scales are used to assess changes in UNS levels including Catherine Bergego Scale (CBS) and Behavioral Inattention Test-Conventional Subset (BIT-C).

The Catherine Bergego Scale, published by Azouvi et al. in 1996, is an ecologically valid screening tool for spatial neglect with excellent reliability and validity (42). The scale is composed of 10 items and each with a score ranging from 0 (normal) to 3 (severe unilateral neglect). According to the scores, three levels of severe neglect can be distinguished as follows: 1–10 (mild neglect), 11–20 (moderate neglect), and 21–30 (severe neglect).

The behavior inattention test-conventional subset consists of the widely used paper–pencil tests (43): (a) line, letter, and star cancellation tests, (b) figure and shape copying, (c) line bisection, and (d) representative drawing. The sum of scores for each test yields a total BIT-C score, ranging from 0 to 146. The cutoff score for the BIT-C test is 129, and a score below 129 is diagnosed as USN, with lower scores indicating more severe neglect.

(a) In cancellation tests, the signs are presented on an A4 (210 × 297 mm) paper, and the participant was required to respectively cross out all lines, all letters “E” and “R,” and all small stars. There is no time restriction. The number of omitted targets is counted. The maximum scores for these subtests are 36, 40, and 54, respectively.(b) In the figure and shape copying, the participant has to copy three figures (a four-pointed star, a cube, and a flower) on a sheet of A4 paper, as well as three figures composed of lines. The maximum score is 4.(c) In the line bisection test, there are three 20 cm horizontal lines on an A4 paper. The participant was asked to search for spatially distributed lines and bisect each line in the middle as accurately as possible. The score ranges from 0 to 3, according to the distance between the mark and the midpoint of each line (0–1 cm 3; 1–2 cm 2; 2–3 cm 1; >3 cm 0). The maximum score is 9.(d) In the representative drawing, the participant should draw a clock, a human, and a butterfly on an A4 paper based on their memory. The score ranges from 0 to 1 for each drawing, according to symmetry, with a maximum score of 3.

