### 2.4. Sample size estimation

In the preexperiment, the changes in BIT-C scores before and after the intervention were 39.33 ± 18.717 for the combined intervention group, 26.33 ± 7.638 for the eye-movement training group, and 20 ± 2.828 for the PA training group. Using the PASS software, the probability α of occurrence of the Type I error was set to 0.05, the probability β of occurrence of the Type II error was calculated as 0.2, the calculation results showed that the combined intervention and eye-movement training groups required 20 samples each, and 9 samples were required for each of the combined intervention and PA training groups. Therefore, taking into account a 10% sample dropout rate, the total sample size was finally determined to be 88 cases, with 22 cases in each group.

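### Two equal primary scales are tested at two visits with no decisive endpoint or success rule, so the 5% level does not hold across the primary family

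*Protocol article*

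**What the plan says.** Section 2.8.2 (Primary outcomes) lists two scales without ranking them: "Two main scales are used to assess changes in UNS levels including Catherine Bergego Scale (CBS) and Behavioral Inattention Test-Conventional Subset (BIT-C". The abstract agrees: "The primary outcome measure will use the Behavioral Inattention Test-Conventional Subset (BIT-C) and Catherine Bergego Scale (CBS) to assess the levels of USN".

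Section 2.8 sets the visits: "This study will measure outcome indicators at two time points: after the end of the intervention and 2 weeks after the end of the intervention". Neither is called primary.

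Section 2.12 (Data analysis) sets the threshold, "2-tailed *P* < 0.05 will be considered a statistically significant difference", and the test: "one-way ANOVA will be used to examine the effectiveness of intervention between the 4 groups at T1, T2, with Bonferroni correction for multiple comparisons". The Bonferroni step is described as a post hoc test following the ANOVA. The Kruskal-Wallis alternative for non-normal data is given with no correction named.

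Section 2.4 (Sample size estimation) uses pilot changes in BIT-C before and after the intervention, and "the probability α of occurrence of the Type I error was set to 0.05, the probability β of occurrence of the Type II error" was set to 0.2. CBS and T2 play no part in it.

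**The concern.** Two scales at two visits make four overall four-group tests, all carrying primary status and each judged at 5%. The only correction stated sits inside each ANOVA, between pairs of groups. It does not reach across scales or visits.

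Two things are at stake. First, the 5% level in section 2.12 does not describe the chance that something in the primary family comes out significant when nothing differs. Second, the plan gives no way to read mixed results. BIT-C is a paper-and-pencil battery, while section 2.8.2 presents CBS as an ecologically valid tool, so the two could well disagree. If BIT-C is positive and CBS is not, or T1 is positive and T2 is not, the same data could be reported as a positive or a negative trial.

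**Working it through.** **1. The plan's own figure.** Section 2.4 gives BIT-C changes of 39.33 (SD 18.717) for the combined arm, 26.33 (SD 7.638) for EMT and 20 (SD 2.828) for PA, with alpha 0.05 and beta 0.2.

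- Combined vs EMT: difference 39.33 - 26.33 = 13.00; SD = sqrt((18.717² + 7.638²)/2) = 14.29. A two-sided pooled t-test needs 20 per group (power 80.0%), which matches the protocol. The normal approximation gives 19.
- Combined vs PA: difference 39.33 - 20 = 19.33. The t-test needs 9 per group (power 82.0%), which also matches.
- Total: 20 × 1.10 = 22 per group; 22 × 4 = 88.

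The sizing therefore reproduces as one scale, one before-to-after change and an undivided 0.05.

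**2. Family-wise rate if independent.** Two scales × two visits = 4 tests. 1 - 0.95⁴ = 18.5%.

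**3. Family-wise rate with correlation.** The protocol gives no correlations, so those below are assumptions. The simulation used the global null, four arms of 20, normal data and 40,000 trials per setting. The correlation between different scales at different visits was taken as the product of the two. The last two columns require a significant F-test and then a Bonferroni-significant difference (six pairs) between the combined arm and at least one other arm, on any scale at any visit.

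| Correlation: visits / scales | Any of 4 F-tests | Combined arm falsely better | Combined arm falsely different, either direction |
|---|---|---|---|
| 0 / 0 | 18.5% | 4.2% | 8.3% |
| 0.5 / 0.3 | 17.2% | 3.8% | 7.5% |
| 0.5 / 0.5 | 16.5% | 3.7% | 7.5% |
| 0.7 / 0.5 | 15.3% | 3.6% | 6.9% |
| 0.8 / 0.5 | 14.7% | 3.4% | 6.7% |
| 0.8 / 0.8 | 12.4% | 2.8% | 5.7% |
| 0.9 / 0.7 | 12.3% | 2.9% | 5.7% |
| 0.9 / 0.9 | 10.3% | 2.3% | 4.7% |

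Over the correlated settings, at least one Bonferroni-significant pair among any of the four arms, after a significant F-test, occurs in about 8% (0.9/0.9) to 13% (0.5/0.3) of trials.

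**4. What the remedies do.**

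- One scale at one visit: 5% for the overall test.
- Both scales at one visit, each at 0.05, either sufficing: 1 - 0.95² = 9.75% if independent, about 7-10% with correlation.
- Four tests at 0.05/4 = 0.0125: 1 - 0.9875⁴ = 4.9% if independent, less with correlation.

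Cost of splitting alpha, BIT-C vs EMT, normal approximation, 20 per group: standard error = 14.29 × sqrt(2/20) = 4.52, and 13/4.52 = 2.876.

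| Alpha (two-sided) | Critical value | Power at 20 per group | n per group for 80% |
|---|---|---|---|
| 0.05 | 1.960 | 82% | 19 |
| 0.025 | 2.241 | 74% | 23 |
| 0.0125 | 2.498 | 65% | 27 |

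**The case against.** The strongest objection concerns which error is counted. The trial's hypothesis (Introduction) is directional and about one arm: the combination does better. An overall F-test says only that some arm differs from some other. To claim that the combination is superior, the combined arm must also win in the Bonferroni comparisons, and that false claim occurs in only about 2-4% of null trials even when all four scale-and-visit tests are allowed. This stands. A reader might infer from four 5% tests that the combination has a 12-18% chance of a false success. The documents do not support that, because it ignores the six-pair correction and assumes a success rule that the protocol never states.

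The objection does not remove the point. Section 2.12 presents the ANOVA itself as the test of effectiveness, so a significant F-test, or a significant pair not involving the combined arm, can be reported as a primary result. The 2-4% also depends on the ANOVA route, since no correction is named for Kruskal-Wallis. It is a global-null figure; settings in which some arms truly differ were not examined.

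It can also be said that testing order belongs in an analysis plan and that the Discussion calls the study preliminary and exploratory. The detail of a testing order can indeed wait. The choice of primary endpoint and visit is a protocol matter, however, and this protocol has made it: two scales, two visits, one undivided level. The same Discussion says that positive results would allow the techniques to be recommended for treatment protocols, so what counts as positive needs a definition.

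**Conclusion.** The point holds as a missing decision rule with an uncontrolled error rate across the primary family. The absence of a decisive scale, visit or success rule follows directly from sections 2.8, 2.8.2 and 2.12 and needs no assumption.

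The size depends on what is counted. Under the global null with 20 per arm, it is about 10-17% for any of the four overall tests (18.5% if independent) and about 8-13% for any Bonferroni-significant pair. For a false claim that the combined arm is better than some other arm it is about 2-4%, or about 5-8% in either direction. All but the independence figure rest on assumed correlations. The upper end needs weakly related visits and scales, which is unlikely in the same patients two weeks apart. The first two ranges should not be presented as the false-success rate of the combination claim. If both scales had to succeed, there would be no inflation across scales, but the protocol states no such rule.

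**What to change.** In sections 2.8.2 and 2.12, and in the abstract, name BIT-C at T1 (end of intervention) as the single primary endpoint, because section 2.4 is sized on it. Make CBS at T1 and all T2 results secondary. This restores 5% for the overall primary test, needs no extra patients and changes only wording. The cost is that CBS loses its equal status.

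If the sponsor prefers to keep both scales primary, there are two alternatives. Either state that both must be significant at T1, or split alpha between them. In both cases the power must be restated. With a split to 0.025, power against EMT on BIT-C falls from about 82% to 74% at 20 per group (normal approximation). Power for CBS cannot be given from this protocol, which reports no CBS effect or SD, so the sponsor would have to supply those figures.
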